**Methods::**

This is an open-label randomized controlled trial with 60 participants divided into 2 study groups in a 1:1 ratio. The intervention group will receive 12 weeks of Guolin Qigong intervention with a 4-week follow-up while control will receive usual care under waitlist. The primary outcome will be feasibility measured based on recruitment and retention rates, class attendance, home practice adherence, nature, and quantum of missing data as well as safety. The secondary subjective outcomes of fatigue, sleep quality and depression will be measured at Week-1 (baseline), Week-6 (mid-intervention), Week-12 (post-intervention), and Week-16 (4 weeks post-intervention) while an objective 24-hour urine cortisol will be measured at Week-1 (baseline) and Week-12 (post-intervention). We will conduct a semi-structured interview individually with participants within 3 months after Week-16 (4 weeks post-intervention) to obtain a more comprehensive view of practice adherence.

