### Sample Size

Using a small effect size (0.2)^
65
^ rather than a medium effect size (0.5)^
64
^ to achieve a more conservative estimation, the sample size is 25 cases in each group with 90% power and two-sided 5% significance trial design.^
88
^ Allowing for a drop-out of about 20% based on previous studies,^89
[Bibr bibr90-15347354241252698][Bibr bibr91-15347354241252698]-92^ a total sample of 60 (30 in each group) would be required.

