## Data Analysis

### Quantitative Data

Data analysis will be conducted by an independent statistician. Data analysis will be by intention to treat using last observation carried forward (LOCF).^
93
^ The normality of the study data will be checked by examining the mean, median, skewness, and kurtosis including graphical representation of the box plot, normal Q-Q Plot or histogram. Continuous data will be summarized using descriptive statistics including the number of observations used in the calculation (*n*), mean, standard deviation (SD), minimum, median and maximum. Categorical data will be summarized as counts and percentages of each category. Between group comparison will be conducted using the t test, chi-square test, or Fisher exact test, as appropriate. We will report the results for two-sided 5% tests for the primary trial outcome. We will use generalized linear mixed model (GLMM). The outcomes of the model will be BFI, PSQI, CES-D scores, and 24-hour urine cortisol test results. Models will include the treatment group as a fixed effect, with time as a random effect to account for the repeated measurements. Analyses will be conducted to identify the baseline characteristics of the participants who may benefit most from the intervention. Model assumptions will be checked and appropriate adjustments to the analysis will be made where necessary. STATA^®^ software version 17.1 (2021; Stata Corporation, College Station, TX, USA) will be used for all analyses. Cohen’s D will be calculated as the absolute differences between the mean change in the variable divided by pooled variance of the change.

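### The article's formula for Cohen's D divides by the pooled variance of the change, not the pooled standard deviation, so the reported effect sizes would depend on the unit of each outcome

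*Protocol article*

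**What the plan says.** The Quantitative Data section ends with a definition of the effect size. Cohen's D "will be calculated as the absolute differences between the mean change in the variable", "divided by pooled variance of the change". Nothing else in the article restates the formula or gives an SD as denominator.

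The same paragraph names four outcomes for the mixed model: BFI, PSQI, CES-D and 24-hour urine cortisol. The article classes these as secondary; the primary outcome is feasibility. Cohen's D is the only standardised effect size that the analysis section names.

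**The concern.** Cohen's d is useful because it has no unit: a difference in score points is divided by an SD in score points, and the units cancel. A variance is in squared points, so dividing by it leaves a number in units of 1/point. Such a number is not Cohen's d, although it would be reported under that name.

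The four outcomes lie on quite different scales. BFI items run from 0 to 10, the PSQI total from 0 to 21 and the CES-D up to 60, while cortisol is a laboratory quantity. Under the stated formula the same standardised effect would give a different figure on each, and the cortisol figure would move with the choice of unit. Anyone who took the published values for ordinary Cohen's d, for example when planning a later trial, would be misled.

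**Working it through.** **Inputs.** The formula and the list of outcomes come from the Quantitative Data section. The scale ranges come from the section on patient-reported outcomes and cortisol. The article gives no SD of change for any outcome and no reporting unit for cortisol, so the SDs below are assumptions, given as ranges.

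The plan has no effect-size figure of its own to reproduce. The sample-size figures do not use this formula and play no part here.

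**Step 1: algebra.** Let Δ be the absolute difference between the groups in mean change, and s the pooled SD of the change.

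- Standard definition: d = Δ / s.
- Formula as written: D = Δ / s².
- Since Δ = d × s, it follows that D = (d × s) / s² = d / s.

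D and d therefore agree only when s = 1. D is too small when s is above 1 and too large when s is below 1. With s = 0.5, for example, a d of 0.5 becomes 0.5 / 0.5 = 1.0.

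**Step 2: change of unit.** Take Δ = 1 and s = 2, so that d = 1/2 = 0.5 and D = 1/4 = 0.25.

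- Multiply every value by 10: Δ = 10 and s = 20. Then d = 10/20 = 0.5, but D = 10/400 = 0.025.
- Divide every value by 10: Δ = 0.1 and s = 0.2. Then d = 0.1/0.2 = 0.5, but D = 0.1/0.04 = 2.5.

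The data are the same and d does not move, yet D ranges from 0.025 to 2.5.

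**Step 3: illustration on the trial's scales (assumed SDs).**

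| Outcome | Assumed SD of change | Δ when d = 0.5 | D as written, d = 0.5 | D as written, d = 0.2 |
|---|---|---|---|---|
| BFI | 1.5 | 0.75 | 0.75/2.25 = 0.333 | 0.30/2.25 = 0.133 |
| BFI | 2.5 | 1.25 | 1.25/6.25 = 0.200 | 0.50/6.25 = 0.080 |
| PSQI | 3 | 1.5 | 1.5/9 = 0.167 | 0.6/9 = 0.067 |
| PSQI | 4 | 2.0 | 2.0/16 = 0.125 | 0.8/16 = 0.050 |
| CES-D | 8 | 4.0 | 4.0/64 = 0.0625 | 1.6/64 = 0.025 |
| CES-D | 10 | 5.0 | 5.0/100 = 0.050 | 2.0/100 = 0.020 |

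Cortisol is left out because any figure would only reflect the unit assumed for it. Step 2 shows what a change of unit does.

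**Step 4: with the denominator corrected.** Dividing Δ by s returns 0.5 (or 0.2) in every row, whatever the SD or unit.

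**Step 5: where the formula enters.** The t test, chi-square test, Fisher exact test and mixed model do not use it. Neither do the 25 per group and total of 60 in the Sample Size section, nor the retention and attendance thresholds (80% to 85% and 75% to 85%) stated with the hypotheses.

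**The case against.** The best reply is that this is a slip of the pen. The statistic is called by its usual name, an independent statistician will do the analysis, and that person may well compute the usual quantity. This is plausible, but it does not remove the error. The article states a specific formula, the same paragraph lists the SD among its descriptive statistics and so knows the term, and nothing tells the reader to substitute one for the other. If the usual quantity is computed, the report departs from the published plan; if the published formula is followed, the figure is wrong. Either way the text needs correcting.

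A second reply is that the article condenses a fuller plan. That would excuse a missing formula, but not one that is stated wrongly.

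A third reply concerns consequences, and it stands. A reader might infer that the error would corrupt a ranking of fatigue, sleep, depression and cortisol by effect size, or a comparison with the small (0.2) and medium (0.5) effect sizes in the Sample Size section. The article plans neither. It uses 0.2 and 0.5 only in sizing the trial, and does not say which outcome or which SD they refer to. Even the corrected statistic, scaled by the SD of change, would match them only if they rest on the same SD.

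It also stands that the means and SDs planned for continuous data would let a reader recompute d, provided they are reported for the change scores. The article does not say that they will be.

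**Conclusion.** The formula is wrong as written. It yields d/SD, which depends on the unit and equals d only if the SD of change is 1. That conclusion is algebra and needs no assumption about the data.

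The size of the distortion cannot be fixed from the document. Under the assumed SDs, a true d of 0.5 would appear as roughly 0.20 to 0.33 for the BFI, 0.125 to 0.167 for the PSQI and 0.05 to 0.063 for the CES-D. These figures show the mechanism and do not forecast this trial's results.

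This should be fixed, but it is not critical. It affects descriptive effect sizes for secondary outcomes and leaves the tests, the sample size and the primary feasibility outcomes untouched. The absolute value in the numerator and the lack of a stated confidence interval are separate matters and do not follow from this error.

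**What to change.** In the last sentence of the Quantitative Data section, replace the words "divided by pooled variance of the change" with: divided by the pooled standard deviation of the change (the square root of the pooled variance).

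The cost is one phrase. Data collection, design, tests and sample size stay as they are. If a fuller analysis plan exists, check that it carries the same correction.

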### Qualitative Data

The researcher will conduct an interview consisting of 6 pre-determined open-ended questions (Refer Supplemental Material 4) that were identified from literature review and based on research questions outlined in the study. Probing questions will only be asked where clarification or expansion of expressed ideas is required. Interviews will be conducted until data saturation is reached. Interview transcripts will be analyzed using the inductive qualitative content analysis approach to provide a comprehensive descriptive summary of the interviewee’s experience and perception of GQ in everyday terms.^
94
^ All audio recordings of the interview will be transcribed verbatim with NVivo or Zoom. First, to obtain an overall impression, the transcribed materials will be read several times thoroughly. Then, sentences or phrases will be condensed and divided into ideas/meaning units. The ideas/meaning units are further condensed, abstracted, and conceived into the categories. All categories will be put together and compared, based on differences and similarities and group together to create themes. This iterative approach to analysis will be conducted until no new ideas/codes emerge and saturation is achieved. A second reviewer will review each phase of the process. A summary of each theme and supporting quotes from participants will be generated and shared with the study team to review independently. Data analysis will be repeated in this manner until a final consensus is reached on final themes to ensure validity.^95,96^ The Consolidated Criteria for Reporting Qualitative Research (COREQ)^
62
^ will be used for reporting the findings.

### Trial Registration and Ethical Issues

This study has been registered with ANZCTR (ACTRN12622000688785p), was approved by Medical Research Ethic Committee of University Malaya Medical Centre (MREC ID NO: 2022323-11092) and recognized by Western Sydney University Human Research Ethics Committee (RH15124).

### Dissemination

The results of this study will be reported in a PhD thesis by the first author and submitted for publication following the rules of CONSORT in a peer-reviewed journal or presentation using de-identified or non-identifiable information. Sensitive information including participants’ details will not be disclosed and will be treated strictly under the privacy and confidentiality act of Malaysia and Australia.

## Discussion

CRF is endemic in cancer survivors with disabling effects on quality of life, co-morbidities, independent living, and work productivity. It includes physiological changes associated with cancer diagnosis and treatment such as cortisol dysregulation, sleep disorders, depression, and functional disability, which further contribute to the burden of CRF. Despite the high incidence of CRF and its symptom clusters involving sleep quality and depression, there is no effective pharmacological intervention to prevent or alleviate these symptoms,^
68
^ highlighting the need to study CRF and its related symptom clusters to understand the common biological mechanisms to improve quality of life of cancer survivors. Numerous studies have reported certain psychological and physiological benefits of Qigong for cancer survivors, promising potential in the realm of cancer medicine. While its definitive impact requires further extensive research, some studies suggest benefits such as enhanced physical functioning, stress reduction, improved mental health, immune enhancement, and improved quality of life, and that it may complement conventional medicine as adjunct therapy by providing a holistic approach to cancer care.^29,33
[Bibr bibr34-15347354241252698][Bibr bibr35-15347354241252698][Bibr bibr36-15347354241252698][Bibr bibr37-15347354241252698][Bibr bibr38-15347354241252698][Bibr bibr39-15347354241252698][Bibr bibr40-15347354241252698][Bibr bibr41-15347354241252698][Bibr bibr42-15347354241252698][Bibr bibr43-15347354241252698]-44^ As research progresses, understanding its potential role in cancer medicine could open doors to more comprehensive and patient-centric approaches to healthcare. In this regard, GQ emerges as a unique mind-body exercise that combines moderate and adaptive walking exercise with a pronounced focus on a specialized breathing technique.^
97
^ While walking has been reported to improve cancer-related symptoms,^57
[Bibr bibr58-15347354241252698][Bibr bibr59-15347354241252698]-60^ the incorporation of breathing technique of GQ serves to foster oxygen-carbon dioxide homeostasis—an essential factor in cancer control and ultimately survival.^60,61^ As such GQ stands as a promising avenue for addressing the cluster of symptoms associated with CRF, encompassing sleep disorder, depression, and alterations in cortisol. However, despite this promising potential, the comprehensive exploration of GQ’s benefits remains a yet untapped opportunity.

Therefore, our hypothesis posits that the current study of GQ is a feasible intervention that holds potential to ameliorate CRF, enhance sleep quality, alleviate depression, and regulate cortisol levels among breast, lung, and colon cancer survivors, while concurrently unveiling a comprehensive spectrum of benefits and barriers related to participation and adherence to GQ training, offering invaluable insights for optimizing and enriching the program.

This is the first mixed-method study comprising a randomized-controlled trial and semi structured interview to evaluate the feasibility and benefits of GQ on CRF symptom cluster among cancer survivors. The quantitative data from the randomized-controlled trial complements the qualitative insights to be obtained through interviews, allowing for a comprehensive exploration of the subjective domains of feasibility, adherence, barriers and participants’ perceptions, experiences of GQ to help improve healthcare and identify factors for enhancing GQ intervention effectiveness.

Moreover, the composition of this multidisciplinary study team comprising experts from Western Medicine and Chinese Medicine integrating their expertise from different perspectives will lead to robust study design, enhanced participant care, rigorous data analysis and comprehensive interpretation of results.

## Limitations

The nature of the intervention precludes blinding of both participants and researcher. While the researcher remains unblinded as this trial is open-label, the instructors will not be aware of intervention allocation to minimize bias. Although including cancer survivors across all stages enables a diverse assessment of feasibility, it potentially limits the generalizability of the results though sub-group analysis will be conducted. Furthermore, the reliance on self-reported data for secondary outcomes emphasizes the necessity for incorporating objective measures like actigraphy, polysomnography, and established scales such as the Hamilton Depression Rating Scale to ensure a comprehensive evaluation of GQ’s impact on CRF, sleep quality, and depression. Additionally, the predominant participation of Asian Chinese individuals highlights the need for expanded research to comprehend GQ’s feasibility and effects among cancer survivors from various ethnic and racial backgrounds. These limitations underscore the challenges inherent in the study’s design and demographics, emphasizing the importance of integrating objective measures and broadening participant diversity for more conclusive and inclusive findings.

Despite the limitations, exploring GQ as a potential intervention to address existing gaps in effective treatment for CRF and its related symptom cluster of sleep quality and depression in cancer survivors demonstrates a forward-thinking approach in the field of oncology. It expands on the knowledge base and promotes innovative thinking, fostering the development of novel interventions with potential contribution to the advancement of oncology care.

## Conclusion

The insights gained from this study may guide future design and implementation of evidence based mind-body interventions to improve cancer survivorship.

